#### On-site Interviews

Participants will be interviewed at baseline, after 6 months, and after 12 months. At each visit, different function domains will be assessed to measure (1) the ability to perform ADLs (eg, personal care, eating, and mobility) and (2) the ability to perform instrumental ADLs (eg, using the telephone, shopping, and managing finances). In fact, the interview implies both a physical evaluation (grip strength, gait speed, and blood pressure) and a cognitive and a psychological assessment. The estimated time for completion is 30 minutes but may vary depending on the participant’s physical and cognitive status. Each of the participants will remain in the study for further follow-up interviews even if he or she is unable to answer, and reasons for incomplete data will be documented by the interviewers. Interviewers may split the visit into 2 parts to respect the participant’s rhythm and to avoid missing data.

During on-site visits, foster caregivers will provide their own sociodemographic data (as well as information on the caregiving burden borne) and those of the elders to be cared for. Thus, both the quality of life of foster caregivers and the main sociodemographic or health data of the participants (eg, medical history, medication, nutrition, and ADL/Instrumental Activities of Daily Living [IADL] performance) are the primary focus of the study.

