#### Secondary Outcomes

The secondary outcomes are as follows:

Length of hospital stays during the 12-month follow-up period, in terms of days and nights, will be collected. The number of consultations with a general practitioner, a medical specialist, or paramedical professional will be reported on the case report forms (CRFs). This information will mainly be collected during interviews with the foster caregiver using the RUD-Lite scale (Resource Utilization in Dementia questionnaire) [17]. This scale assesses the use of health care resources by people with dementia. The foster caregiver will complete this questionnaire at baseline and at subsequent follow-up visits (T3, T6, T9, and T12).Global cost of hospitalization will be retrieved from the local PMSI databases.Vital status (alive or deceased) will be collected at T3, T6, T9, and T12.For the diagnosis of lower respiratory tract infections, at least two of the following symptoms must be present and a doctor must confirm the clinical evidence: (1) cough (starting or worsening), which may produce phlegm; (2) specific clinical signs during auscultation; (3) fever (≥38 °C); (4) chest pain; (5) rapid, shallow breathing (≥25 per minute); and (6) confusion or increased dependency [16].Geriatric syndromes [18] in participants will be assessed at T0, T6, and T12 as follows:Frailty will be assessed using Fried’s phenotype [19], that is, 5 predefined physical frailty criteria such as weight loss, slowness, low physical activity, weakness, and exhaustion. This will be analyzed as a dichotomous variable, that is, 1=frail and 0=not frail.The level of cognitive deterioration of the participants will be assessed using the Mini-Mental State Examination (MMSE) [20,21]. This 30-item scale assesses the severity of cognitive deterioration through items such as orientation, learning, attention, arithmetic, memory, language, and constructive praxis. The scale is rated from 0 to 30, reflecting the level of cognitive impairment.Depression will be assessed using the Center for Epidemiologic Studies—Depression Scale (CES-D) [22] validated in French by Fuhrer and Rouillon [23]. This 20-item questionnaire assesses depressive symptomatology, including 4 positive polarity items (happiness, self-worth, confidence, and enjoyment). The frequency of symptom occurrence during the past week is assessed by the participant using a 4-point Likert scale (never, occasionally, quite often, and frequently). The score ranges from 0 to 60. The higher the score, the more significant the symptomatology. High depressive symptomatology corresponds to a score above 16. Data will be collected at baseline, T6, and T12. For statistical analyses, the variable will be dichotomized (1=presence of depression and 0=absence of depression).The total number of medications taken by participants will be collected directly from the RUD-Lite questionnaire, at T0, T3, T6, T9, and T12, to assess polypharmacy.The total number of falls since the last visit will be collected at each follow-up from the foster caregivers.The Short Physical Performance Battery [24,25] will help to assess sarcopenia. Three subtests measure lower-extremity functions: keeping balance (feet side-by-side, semitandem, tandem balance position, to be kept for 10 s each); walking 4 m at usual pace, yielding a gait speed ratio (meter per second); standing up and sitting down 5 times as quickly as possible with the arms folded. Each movement is scored 0-4 points out of a total score from 0 to 12, with higher scores showing better physical performance. If the total score is below 8, there is a risk of sarcopenia. For the analyses, the variable will be dichotomized accordingly (1=sarcopenia; 0=no sarcopenia).Undernutrition will be assessed with the short version of the Mini Nutritional Assessment [26]. This questionnaire assesses nutritional status. A score below 12 indicates probable undernutrition. For the analyses, the variable will be dichotomized accordingly (1=undernutrition; 0=no undernutrition).Sensory impairments (audition and vision) will be collected by directly asking the foster caregiver. Variables will be dichotomized accordingly (1=hearing/vision impairment; 0=hearing/vision impairment).The level of independence in ADL and incontinence will be assessed using the Katz scale [27], a 6-item scale assessing independence in 6 basic ADLs: bathing, toileting, transferring, eating, dressing, and incontinence. For each activity, a score of 1 indicates complete autonomy, a score of 0.5 indicates partial autonomy, and a score of 0 indicates complete dependency.The level of independence in IADL will be assessed using the Lawton IADL scale [28]. The Lawton IADL scale measures 8 items: using the telephone, shopping, preparing food, housekeeping, doing laundry, using transportation, handling medications, and handling finances. The score is from 0 to 8; a score of 8 indicates total autonomy, and 0 indicates total dependency. In France, the Autonomy, Gerontology Iso-Resources (AGGIR) questionnaire has been developed by public authorities to quickly assess the degree of dependency of elderly people and assign a dependency group, ranging from 0 (bedridden, completely dependent) to 6 (no help required, the person is autonomous in everyday activities).Psychological and behavioral symptoms in dementia will be assessed with the short version of the NeuroPsychiatric Inventory or NPI [29,30]. This scale assesses the psychological, behavioral manifestations (agitation, hallucinations, apathy, etc), neurovegetative symptoms (sleep and appetite), and the impact on the professional’s workload.Feeling of loneliness will be captured with the 14th item of the CES-D [22,23]: I felt lonely. The answer possibilities are never, occasionally, often, and frequently. The answer “often” or “frequently” indicates a feeling of loneliness.Risk of developing pressure ulcers will be assessed with the Braden scale, and pressure ulcers will be classified according to the National Pressure Ulcer Advisory Panel, European Pressure Ulcer Advisory Panel, and Pan Pacific Pressure Injury Alliance [31].Quality of life and adaptation will be assessed as follows:Quality of life of the participant will be assessed at baseline, T6, and T12 using the Questionnaire Quality of Life—Alzheimer’s Disease (QoL-AD) [32,33]. This 13-item questionnaire assesses the participant’s physical condition, mood, relationships with friends and family, financial difficulties, and overall quality of life. The questionnaire is to be administered to both seniors and caregivers, and thus is based on both self-rated health problems and proxy ratings from foster families. The items are evaluated using a 4-point ordinal scale ranging from poor to excellent, with a total score ranging from 13 to 52. For the weighted score, the participant’s score is multiplied by 2, the caregiver’s score is added, and the total is divided by 3 to bring the score back to the initial scale. In the proxy version, the foster caregiver will be asked to try to give the answer they think the participant would give.Health-related quality of life of the participant will be assessed with the EQ-5D questionnaire [34]. This questionnaire assesses health conditions. It is the most widely used questionnaire in medicoeconomic analyses. It allows health outcomes to be assessed in terms of quality-adjusted life-years (QALYs). This indicator summarizes the length and quality of life in a single figure. The result of a cost-utility analysis is expressed in terms of the cost of gaining one QALY (ie, 1 year lived in perfect health). To estimate QALY, health-related quality of life is designed on a continuum from 0 (death) to 1 (perfect health). Each health status is thus assigned a weight of 0 to 1; the higher the score, the higher the corresponding quality of life.On the first page, the participant has to indicate, for each of the 5 dimensions assessed (mobility, independence, routine activities, pain or discomfort, and anxiety or depression), the state in which he or she finds himself or herself, by choosing 1 of the 3 options with increasing severity: no problems, problems, and extreme problems. The answers can be combined to describe the residents’ health status, using a 5-digit number corresponding to the 5 answers.On the second page, the participant assesses his or her overall health using a standard vertical 20 cm visual analog scale (EuroQol visual analog scale), graduated from 0 to 100, from “best imaginable state of health” to “worst imaginable state of health.”The score will be collected at T0, T6, and T12. The interviewer will use both the participant version and the proxy version. In the proxy version, the foster caregiver will be asked to try to give the answer they think the participant would give.Adaptation to the nursing home setting will be assessed at baseline, T6, and T12 using the Castonguay and Ferron scale [35]. This is a 17-item scale designed to identify who do not experience a favorable adaptation to the living conditions in nursing homes. The participants answer yes or no to a series of statements about their daily life and habits in the residence. A score of 16 or 17 indicates a good general adaptation to life in the residence, whereas a score of 11 or less indicates significant difficulties.Foster caregivers’ quality of life will be assessed with the Medical Outcomes Study Short-Form General Health Survey—36 items (SF-36) [36], a widely validated health-related quality of life questionnaire that uses questions on physical, social, and psychological domains.Symptoms of burnout will be assessed with the Professional Quality of Life (Pro-QoL) scale [37]. This 30-item questionnaire yields 3 domain-specific scores: compassion fatigue (ie, the pleasure of being able to do your job well), work satisfaction, and burnout in helping professionals.

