### Data Analysis

First, the analysis will describe the number of included participants, the inclusion curve (evolution of the number of people included between the first and last inclusion), the number of theoretical visits, the number of visits actually made, and the ratio of both (number of visits made or number of theoretical visits).

A description of the rate and causes of death and study dropout will also be provided.

The following quantitative variables described in terms of number of staff, mean, and interindividual SD and 95% CI of the mean, median, range, and IQR values: number of hospitalizations, total length of hospitalization, total cost related to hospitalizations, total number of consultations with a general practitioner, total cost of low respiratory infections, total number of falls, MMSE score, total number of drugs, NPI score, QoL-AD score, SF-36 score, and Pro-QoL score.

Qualitative variables (ordinal: AGGIR grid, feeling of loneliness; dichotomous: vital status; presence or absence: frailty syndrome, depression, undernutrition, visual impairment, hearing impairment, incontinence, ADL dependency, IADL dependence) of participants at inclusion will be described in terms of frequency and number.

Comparisons between the 3 times (T0, T6, and T12) will be performed using repeated-measures ANOVA for quantitative variables and the Cochran-Armitage test for trend for qualitative variables.

Statistical analyses will be performed using the RStudio software (version 2.7; Posit Software).

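### Change across T0, T6 and T12 in binary and ordinal variables is tested with Cochran-Armitage, which ignores that the same residents are seen each time and is undefined for AGGIR

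*Protocol article*

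**What the plan says.** The Data Analysis section fixes one rule for change over time: "Comparisons between the 3 times (T0, T6, and T12) will be performed using repeated-measures ANOVA for quantitative variables", and for the rest "the Cochran-Armitage test for trend for qualitative variables". It makes no exception by type of qualitative variable.

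The same section lists the qualitative variables. It starts with "ordinal: AGGIR grid, feeling of loneliness; dichotomous: vital status" and goes on to present/absent items: frailty, depression, undernutrition, visual and hearing impairment, incontinence, and ADL and IADL dependency.

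On who is measured at each wave, On-site Interviews says "Participants will be interviewed at baseline, after 6 months, and after 12 months", and adds "Each of the participants will remain in the study for further follow-up interviews even if he or she is unable to answer". The waves are therefore repeated measurements of one cohort.

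On the two ordinal variables, Secondary Outcomes describes AGGIR as "ranging from 0 (bedridden, completely dependent) to 6" and gives no cut-point. For loneliness it says "The answer possibilities are never, occasionally, often, and frequently", then supplies a yes/no rule that counts the two most frequent answers as lonely.

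**The concern.** The Cochran-Armitage test compares a binary proportion across independent ordered groups. Two of its conditions are not met.

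- **Independence.** The groups here are the same people at three times. The test's variance leaves out the covariance between a resident's own values, so it is too large whenever that covariance is positive. The sentence respects the pairing for quantitative variables and drops it for qualitative ones.
- **Outcome type.** The test is defined for a 2 x k table. AGGIR as listed is not binary.

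The abstract's Conclusions and the Discussion both say the outcomes will allow the evolution of geriatric syndromes to be assessed. For the syndromes held as present/absent, this is the only comparison over time that the section states. A real change could be missed and read as stability in foster care.

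**Working it through.** **The plan's own figure.** The article computes nothing for the trend test. Its only calculated figures are the CI half-widths in Study Sample, and they reproduce: 1.96 x sqrt(0.15 x 0.85/250) = 4.4% and 1.96 x sqrt(0.30 x 0.70/250) = 5.7%. They concern the primary outcome and are not in question.

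**Inputs.** From the documents: three waves of the same residents; 109 recruited (Results); 5% level (Study Sample, read as two-sided). Assumed: exchangeable within-resident correlation rho, shown over a range, and the prevalences in the power example.

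**Size with no change.** Take scores -1, 0, 1 and n residents seen at all waves. The trend statistic reduces to T = n x (prevalence at T12 - prevalence at T0).

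- Variance used by the test: 2n p(1-p).
- True variance: 2n p(1-p)(1-rho).
- Actual two-sided size: 2 x [1 - Phi(1.96/sqrt(1-rho))].

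| rho | 1.96/sqrt(1-rho) | actual size |
|---|---|---|
| 0 | 1.96 | 5.0% |
| 0.2 | 2.19 | 2.8% |
| 0.3 | 2.34 | 1.9% |
| 0.4 | 2.53 | 1.1% |
| 0.5 | 2.77 | 0.6% |
| 0.7 | 3.58 | 0.03% |

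Simulation at prevalence 30% and n = 109 agrees: 1.8% at rho 0.3, 0.7% at 0.5 and 0.05% at 0.7. With 10% dropout per wave the sizes are 2.3%, 0.75% and 0.2%. A trend test with within-resident variance stays between about 4.3% and 5.4%.

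**Power, assumed 40%, 46%, 52%, n = 109.**

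- Mean of T: 109 x 0.12 = 13.08.
- Cochran-Armitage critical value: 1.96 x sqrt(2 x 109 x 0.46 x 0.54) = 14.42.
- True variance of T: 109 x [0.24 + 0.2496 - 2 rho x sqrt(0.24 x 0.2496)]. This gives an SD of 6.53 at rho 0.2, 5.66 at 0.4 and 4.00 at 0.7.
- Cochran-Armitage power: 1 - Phi((14.42 - 13.08)/SD).
- Paired T12-T0 contrast power: Phi(13.08/SD - 1.96).

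| rho | Cochran-Armitage | paired contrast |
|---|---|---|
| 0.2 | 42% | 52% |
| 0.4 | 41% | 64% |
| 0.7 | 37% | 91% |

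Simulation gives 39% against 63% at rho about 0.4, and 36% against 91% at about 0.7.

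**Outcome type.** AGGIR, 0 to 6 as written, by three waves is a 7 x 3 table. Loneliness with four answers is 4 x 3. The named test applies to neither in that form. Loneliness becomes 2 x 3 if the yes/no rule in Secondary Outcomes is used; nothing equivalent is given for AGGIR.

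**Vital status.** Every resident is alive at T0 and death is irreversible, so a three-wave trend in prevalence has no useful meaning for it.

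**The case against.** The strongest reply is that this is a descriptive cohort whose primary outcome is hospitalization. The stated objective for geriatric syndromes is prevalence, and a conservative secondary test creates no false-positive claim. That stands and limits the weight of the point. It does not make the named test suitable for the comparison the section assigns to it.

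Four stronger readings are tempting, and the documents do not support them.

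- A reader might infer that no syndrome gets a sound analysis over time. Falls, number of drugs and MMSE score are listed as quantitative and go to repeated-measures ANOVA.
- A reader might infer that neither ordinal variable can be tested. That is firm only for AGGIR. For loneliness the problem is a mismatch between the ordinal label in Data Analysis and the yes/no rule in Secondary Outcomes, plus the same pairing defect as the binary variables.
- A reader might infer that the test is severely conservative for every variable. No correlation is given. At rho 0.2 to 0.3 the loss is moderate, and fluctuating states such as loneliness or depressive symptoms may lie there. Persistent states such as incontinence, dependency or sensory loss plausibly lie higher, but that too is an assumption.
- A reader might infer that the primary result is at risk. The hospitalization rate and its CI do not use this test.

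The power example also assumes all 109 residents are seen at all waves, whereas the plan itself expects deaths and dropouts. The dropout simulation shows that the size result barely changes.

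**Conclusion.** The point holds as a defect in a stated secondary analysis. The test named for qualitative variables does not fit repeated measurements of the same residents. Its direction of error, too few rejections, follows for any positive within-resident correlation and does not depend on the assumed values. Its size does: from moderate (2.8% instead of 5% at rho 0.2) to nearly never rejecting under no change (0.03% at rho 0.7). The shortfall in power against a paired contrast runs from about 10 to over 50 percentage points in the example. For AGGIR the test is undefined as the plan stands. This should be corrected before the secondary analyses are reported, but it does not undermine the study's main objective.

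**What to change.** In Data Analysis, replace the Cochran-Armitage clause with a within-resident method:

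- **Binary variables:** logistic GEE with time (T0, T6, T12) as the factor, or Cochran's Q if a simple test on complete cases is preferred. GEE leads directly to a change in prevalence; a mixed logistic model would give resident-specific odds ratios instead.
- **AGGIR, and loneliness if kept ordinal:** a cumulative-logit GEE or mixed model, or a Friedman test on complete cases. If loneliness is to be analysed with the yes/no rule, say so in Data Analysis and treat it as binary.
- **Reporting:** give the change in prevalence with its 95% CI alongside any p-value.
- **Vital status:** remove it from this comparison and report mortality as incidence or survival.

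The cost is a few lines of text and standard R code. No new data are needed. The article says analyses are ongoing, so the change should be recorded as an amendment to the stated method.

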### Quality Control

During the study, quality control will be carried out by the project manager and the clinical research assistant. All interviewers will be required to attend training on data collection and data reporting. Under no circumstances should the names or addresses of the individuals concerned be made clear.

The electronic CRF will allow single data entry, which will be double checked by the investigators. Data management will be performed using the Capture System software (Clinsight). The Clinsight web-based module will allow remote access to the database, with a 128-bit SSL encryption. Each interviewer will have a personal and unique name and access code that will allow him or her to enter and correct data—everything is documented and saved every day on another server.

### Ethics and Dissemination

The KASAF is an observational study involving human participants without any identified risk for the participants’ safety. In accordance with this status, the need for a signed consent form has been waived off by the regulating bodies (law 2012-300). Residents will be provided with an information leaflet outlining the key points of the study. Participation is voluntary and residents can refuse to participate or discontinue participation at any time without prejudice. Considering the high proportion of family foster residents with cognitive impairment, the on-site investigator will ensure that the residents have understood the implications of their participation. If the resident is under guardianship and/or is unable to understand, nonopposition from the legal guardian or a documented contact person will be sought as well.

Nonopposition or opposition will be documented in the participant’s medical file.

This study will be carried out in accordance with state laws regulating research involving human participants and with the Helsinki declaration.

The KASAF was registered under the RGB-ID number 2020-A00620-39 and was approved by the French Sud Méditerranée III Ethics Committee on July 1, 2020. Data analysis will be performed on-site (University Hospital, Guadeloupe). All documents related to this research will be archived for 15 years after completion of the study.

## Results

Recruitment opened in September 2020 and ended in May 2021, with 109 older people recruited and 56 respective foster caregivers. The 1-year follow-up was ended in June 2022. Data analyses are ongoing, and the first results are expected to be published in May 2023.

## Discussion

Foster families are a potentially innovative way to accommodate older people with dependency. Epidemiological data from the study will describe the clinical characteristics of older people in foster families. Beyond mortality and morbidity, the numerous outcomes will allow assessing the evolution of geriatric syndromes over time. In addition, this study will also look at the sociodemographic profile of foster family caregivers—who are not necessarily health professionals—in terms of age, life course, quality of life, or burnout. It may offer a basis for specific training courses and help the authorities to better characterize the requirements an applicant must meet to become a fully-fledged foster caregiver.

This descriptive study could help define the place of the foster family in the transition from frail elderly to dependent elderly status. Indeed, foster family could also be an intermediate stage between home care and nursing home care. The epidemiological data obtained will be compared with data from other management systems. In this perspective, we will conduct a twin study in nursing home, the KArukera Study of Aging in EHPAD (KASEHPAD) study, which will take place in 14 nursing homes in Guadeloupe. Both studies will have similar designs and objectives. The protocol for the KASEHPAD study has been registered on ClinicalTrials.gov (NCT04587466). If patient characteristics are similar, it will be possible to compare mortality, hospitalization rates, and all variables of interest, including cost of care, between these 2 care settings. Depending on the profile of the KASAF’s participants, we could also compare foster care with home care or residential care facilities [38]. The collection of epidemiological data in foster family is therefore an essential step to carry out randomized studies between these different care pathways, with the aim of determining the most effective and efficient care.

Foster families have never been formally assessed, the most robust results dating back to 30 years. In theory, it is less expensive than nursing homes for the community, but in the absence of scientific studies on the associated health outcomes (number of hospitalizations, deaths, etc), this model has not been validated and remains rare in metropolitan France. Yet, foster caregivers could be valuable assets in health care, thanks to their intimate knowledge of older persons and their pathologies, compared with nursing home staff, which have a high turnover, thus reducing avoidable hospitalizations and medical consultations.

Moreover, in the event of a health crisis such as the one experienced with the COVID-19 pandemic, measures of isolation and social distancing are much easier to implement, as foster family residents live in small family units, usually have single rooms, with less comings and goings than in nursing homes. The collected data will be used for exploring the characteristics of the foster home residents with aims that might not be considered today (1) because they are out of topic and (2) because science evolves.

This study presents limitations. We will not have access to data from informal caregivers, who could provide different insights on the participant’s state of mind or daily life. Also, cost analyses will focus only on hospitalization costs. This is why an ancillary study will be carried out after the end of the KASAF, using information from the national health insurance database. This study will accurately assess the cost of the entire health care pathway, including nursing, medical transportation, and other health care expenses. Finally, the KASAF does not include randomized interventions versus nursing home limiting causal interpretations of the results.

We hope that our results will help introduce more rationality into social and economic debates, sometimes led by accounts of personal experiences and extrapolated indicators, often for lack of robust data, and help ensure that public health policies are based on sound scientific evidence. Indeed, our data will be used to support the coordination of institutional funding bodies, especially resource allocation.

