
Foster families have also been tried out in others countries (eg, United States, Belgium, Italy, Russia, and Finland), but few scientific studies have assessed its effectiveness and efficiency. A Cochrane meta-analysis published in 2015 compiled 10 studies comparing home care or foster care with nursing home care for 16,377 older participants [12]. Because of the methodological limitations of the studies included, the meta-analysis failed to determine whether or not this type of accommodation was the most efficient in terms of mortality reduction, physical function, quality of life, or hospitalization rates. Indeed, the available studies relied on small samples and had high risks of bias (design bias, evaluation bias), and the baseline characteristics of the participants were very heterogeneous. Three 30-year-old studies focusing on foster care in the United States were included [13-15]. Two of them are of interest [13,15]. Braun and Rose [13] compared 269 older participants: 100 lived in foster care, 101 in nursing homes, and 68 at home. After 3 months, Activities of Daily Living (ADL) scores only improved in the foster care group, and costs were lower than those for the other 2 groups (US $28 per day vs US $74 for nursing homes and US $45 for home). There was no difference in morbidity, defined as the number of infections, injuries, skin problems, and hospitalizations. In their randomized study on 112 participants in foster care or nursing homes, followed for 12 months, Oktay and Volland [15] found no difference in mortality rates between settings (32.0% vs 28.8%). Stabilization or improvement of ADL and cognitive status, as well as overall lower health care expenses (25% less), was in favor of foster care. Nevertheless, nursing home residents’ level of satisfaction compared favorably with that of foster family residents. In any case, available data are scarce, assessed with short follow-ups, lack essential clinical outcomes, and definitely need to be updated.

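### The trend test named for yes/no syndromes treats T0, T6 and T12 as independent groups, so change in residents is mixed with loss of residents through death

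*Protocol article*

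**What the plan says.** Data Analysis names one method for comparing qualitative variables across T0, T6 and T12: "the Cochran-Armitage test for trend for qualitative variables". The yes/no variables it lists are "presence or absence: frailty syndrome, depression, undernutrition, visual impairment, hearing impairment, incontinence, ADL dependency, IADL dependence". Frequency tables for these are specified at inclusion, so the trend test is the only analysis over time that the article names for them.

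Under Secondary Outcomes, geriatric syndromes "in participants will be assessed at T0, T6, and T12 as follows". This is one cohort measured three times. Frailty is coded frail or not frail, with no category for death.

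Death appears in Data Analysis as a separate item: "A description of the rate and causes of death and study dropout will also be provided". Under On-site Interviews, living residents who cannot answer stay in follow-up, so the selection at issue is mainly through death.

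The Discussion states the intended use: "the numerous outcomes will allow assessing the evolution of geriatric syndromes over time".

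**The concern.** The Cochran-Armitage test asks whether a proportion changes across ordered, independent groups. Applied to three waves of one cohort, it has two faults.

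- It ignores that each resident is compared with himself or herself.
- The groups differ in who is in them, because residents who have died contribute to T0 but not to later waves.

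If residents with a syndrome die more often than those without it, the share affected among those still observed drifts down even when no resident changes. New cases can be offset by deaths of existing cases, and the result then reads as stable.

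The Introduction counts stable or better ADL status in a cited study as favouring foster care, so a flat or falling share here could well be read as benefit. The Discussion also foresees comparing all variables of interest with a twin nursing-home study. If mortality differed between the two settings, the shares among survivors could differ for that reason alone.

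**Working it through.** **The plan's own figure.** The article gives no precision or power for syndrome change. Its only such figure concerns the hospitalization rate, and it reproduces: 1.96 × √(0.15 × 0.85 / 250) = 4.4% and 1.96 × √(0.30 × 0.70 / 250) = 5.7%. It does not bear on this point.

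**Inputs.**
- One-year mortality m: 30%, rounded from the 32.0% and 28.8% that the Introduction reports for a randomized study of foster care or nursing homes. Lower values (20%, 10%) are shown as a range.
- Share affected at T0, p = 60%: assumed.
- Ratio of death risk, affected to unaffected, RR = 1 to 3: assumed.
- No survivor changes state, so true change within residents is zero.

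**Formulas.** Risk of death in the unaffected: q = m / (p × RR + 1 − p). Share affected among survivors: p(1 − RR × q) / (1 − m).

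**With m = 30%.**
- RR 2: q = 0.30 / 1.6 = 0.1875. Affected survivors 0.6 × 0.625 = 0.375; unaffected survivors 0.4 × 0.8125 = 0.325. Share = 0.375 / 0.70 = 53.6%.
- RR 3: q = 0.30 / 2.2 = 0.136. Affected survivors 0.6 × 0.591 = 0.3545; unaffected survivors 0.4 × 0.864 = 0.3455. Share = 0.3545 / 0.70 = 50.6%.

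Share affected at T12 (%), starting from 60%:

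| Mortality | RR 1 | RR 1.5 | RR 2 | RR 3 |
|---|---|---|---|---|
| 30% | 60.0 | 56.0 | 53.6 | 50.6 |
| 20% | 60.0 | 57.7 | 56.25 | 54.5 |
| 10% | 60.0 | 59.0 | 58.3 | 57.6 |

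**Onset that could be hidden.** For the share to read 60% again at m = 30%, affected survivors must reach 0.6 × 0.70 = 0.42.
- RR 2: (0.42 − 0.375) / 0.325 = 13.8% of surviving unaffected residents become affected.
- RR 3: (0.42 − 0.3545) / 0.3455 = 18.9%.

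**How the test behaves.** 20,000 cohorts were simulated with 50% affected at T0, 32% mortality and the test applied to those alive at each wave.
- Nobody changes state: the T12 share is 42.2% (RR 2) or 38.2% (RR 3), below T0 in at least 99% of cohorts. A significant downward trend appears in 2.4% (RR 2) or 19.9% (RR 3) of cohorts of 109, and in 20.2% or 84.2% of cohorts of 250.
- 10% new onset per 6 months, 109 residents: at RR 3 the share is flat (50.0% to 49.3%) although about 7.7 of 73 survivors worsened. At RR 2 it rises to 52.7%.
- No deaths, 10% onset balanced by 10% recovery per 6 months, 109 residents: the test rejects in about 0.1% of cohorts at a nominal 5%. Ignoring the pairing makes it far too conservative.

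**The same example with pairing.** If no survivor changes state, residents assessed at both T0 and T12 have no discordant pairs, and McNemar's comparison shows zero change. Pairing removes the false fall.

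**The case against.** Several points on the other side stand.

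- The stated objective is the prevalence of geriatric syndromes, and a trend in prevalence is one ordinary meaning of evolution. A reader might infer that the article promises estimates of individual frail-to-dependent transitions, because the Discussion mentions "the transition from frail elderly to dependent elderly status". It does not. That sentence says only that the study could help define the place of the foster family in that transition, and the next one explains this as a care setting between home and nursing home.
- The article condenses a fuller plan that is not shown. One can say that it names no analysis linking death to syndrome status, but not that none exists. That the test uses only those still observed is inferred from the test, not stated.
- The size rests on assumptions. The article gives no syndrome prevalence and no death ratio, the mortality comes from a study it calls 30 years old, and zero new onset is an extreme case in dependent older people.
- At 109 residents a significant false decline is uncommon unless selection is strong.

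The last two limit the size but do not remove the fault. The study is descriptive, so the shifted proportion is itself what gets reported, significant or not. The choice of test is stated in the article rather than left open, and it does not fit repeated measurements on the same residents.

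A reader might also infer that no paired test would help. The worked example shows otherwise. What pairing leaves open is the fate of those who died, so death must be reported beside it.

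**Conclusion.** The point holds as a mismatch between a stated method and the data. Followed as written, the Cochran-Armitage comparison mixes change in who is alive with change in residents, and it ignores the pairing.

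Under the assumptions above (60% affected, 30% mortality, death ratio 2 to 3, no change of state), the false fall is about 6 to 9 percentage points. At 20% mortality it is about 4 to 5.5 points. The direction is conditional: no bias if affected and unaffected residents die equally often, masked worsening if there is moderate new onset, and a rising share if onset is high enough. It would be too strong to say that the planned analysis will show improvement, or that the article claims transitions it fails to estimate.

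**What to change.** In Data Analysis, for yes/no syndromes:

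1. Replace the Cochran-Armitage test with a paired or longitudinal binary method. Examples are McNemar's test for T0–T6 and T0–T12 among residents assessed at both visits, or a GEE or mixed logistic model over the three visits. Label the result as change among survivors.
2. Beside it, report for each syndrome, with number, proportion and 95% CI: T0-negative residents with new onset, T0-positive residents who recovered, and those in each T0 group who died or were not assessed.

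A combined frailty and ADL state is not needed as a main result. The article gives no cut-off for ADL dependency, and ADL-independent cells may be nearly empty in a dependent cohort.

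The cost is revised wording and a few tables, since syndromes and vital status are already recorded per resident. The downside is precision. At 109 residents and 30% mortality, the illustration leaves 109 × 0.325 ≈ 35 to 109 × 0.3455 ≈ 38 surviving unaffected residents. Onset in 5 of 35 has a 95% half-width of about 1.96 × √(0.143 × 0.857 / 35) ≈ 12 points. Intervals will be wide, and the report should say so.
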